# STUDY INTERVENTION

## Description

We plan to adapt and evaluate a d-DBT skills intervention developed by Linehan et al. in the USA for individuals with suicidality and severe alcohol use (61). d-DBT was acceptable, safe, and effective in reducing suicidal ideation, substance use, and emotion dysregulation (61). Our group have recently adapted d-DBT and delivered this as a trans-diagnostic intervention to individuals hospitalized to psychiatric inpatient departments. The d-DBT intervention consists of eight modules delivered over 8-weeks. Adaptation in the present study will focus substance use to include cannabis, as this is the most used recreational substance in the CHR population (16). Skills like “dialectical drinking” will be adapted to focus on cannabis use and substance use more broadly (Table 1). Our youth advisory council will be consulted on the youth friendly language and provide input on adaptation of the intervention.

## Treatment Regimen

The first two modules will focus on mindfulness skills (“What” and “How” skills), the following two modules are focused on reducing problematic substance use (“Dialectical Drinking,” “Clear Mind,” “Community Reinforcement,” and “Burning Bridges”), the subsequent three modules are focused *
[figure not shown]
*on increasing emotion regulation strategies (“Model of Emotions,” “Check the Facts,” “Opposite Action,” “Problem Solving,” “Building Mastery,” and “Cope Ahead”), and finally, the last module includes skills on tolerating distress (“TIP” & “Distract”) (Table 1).

[figure not shown]
Each session includes 2–3 new DBT skills. Each new skill will first be introduced via a 3 to7-minute video segment delivered by Marsha Linehan. After the video, participants will be directed to a “Key Point” page in which they will be presented with the salient aspects from the video. Finally, participants will engage in the skill through an interactive and guided practice. At the end of each session, participants will select a homework practice. These homework assignments will be embedded in the newly adapted d-DBT platform and are intended to be completed prior to the next module. Each session lasts approximately 30–50 minutes. At the end of each session, there will be a link to a brief survey where participants will confirm their completion of the module. Every week, a member of the research staff will check-in with the participants via phone or video platform (patient preference) to enhance adherence and trouble-shoot any issues related to the intervention.

Table 1. Modules and the main skills included in d-DBT.

| Module 1-2 Mindfulness skills: | “What” skills: these are ‘what’ you are doing while practicing mindfulness. They are ‘observe’, ‘describe’ and ‘participate.  “How” skills: these are ‘how’ you practice mindfulness. They are non-judgmentally, one-mindfully, and effectively. |
| --- | --- |
| Module 3-4 Substance use skills: | Clear Mind: Clear mind represents the synthesis between clean mind and addict mind. In clear mind, you are clean, while at the same time you stay aware of the dangers of relapse and actively engage in behaviors to prevent a lapse or relapse  Burning Bridges: Burning bridges involves reducing your opportunities to engage in the addictive behavior. Basically, you're burning the bridge between you and people, places, or events in your life that encourage or facilitate addiction or maladaptive behaviors  Dialectical Drinking. The skill of dialectical drinking describes the abstinence violation effect, goal setting, pros and cons of maintaining or changing their drinking behavior, as well as an assessment of motivation and confidence to follow-through on their drinking goal. We plan to adapt this module to focus on cannabis use and substance use more broadly. |
| Module 5-7 Emotion regulation skills: | Model of Emotions: breaks down your emotional experience into 6 parts. Changing any one part can change the entire response.  Check the Facts: helps you change your emotional response and make healthier decisions as a result. Using check the facts, you can modify your response to a level that is appropriate for the situation, or respond with a more fitting emotion  Opposite Action: is a deliberate attempt to act opposite of your emotion urge. If your emotions are doing more harm than good, try acting opposite  Problem Solving: is a skill to do a behavioral analysis, assess what can be changed, brainstorm alternatives, and practice putting into action.  Building Mastery: A skill that helps improve self-esteem and confidence.  Cope Ahead: is skill about making a plan for ourselves for dealing with a stressful situation we will encounter in the future |
| Module 8 Distress Tolerance Skills | TIP: A distress tolerance skill that is an acronym that stands for Temperature, Intense Exercise, Paced Breathing, and Progressive Relaxation. TIP skills ask that we change our body chemistry to regain control of our emotions and behavioral responses.  Distract: a group of distraction techniques for distress tolerance |

Duration of treatment and follow up: The d-DBT intervention will be delivered over 8 weeks and participants in the experimental arm will be asked to complete 1 module per week. Measures will be completed at study entry and repeated immediately post-treatment at 8 weeks.

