# CLINICAL TRIAL OBJECTIVES

## Specific Aim 1

To adapt an existing, d-DBT intervention for use in young people at CHR for psychosis. **H1:** d-DBT can be clinically adapted and refined in a developmentally appropriate way for virtual use among CHR individuals.

## Specific Aim 2

To evaluate the acceptability of the d-DBT invention and the feasibility of conducting a fully powered randomized controlled trial (RCT) of d-DBT in individuals at CHR for psychosis. **H2:** d-DBT will be acceptable to CHR individuals as demonstrated by qualitative feedback, attendance rates of d-DBT sessions, the Client Satisfaction Questionnaire (CSQ) and the System Usability Scale (SUS). d-DBT for CHR individuals will be feasible as demonstrated by our ability to recruit our desired sample of 60 participants and retain 80% of those recruited by the end of the 8-week study period. Participants’ ability to complete the clinical assessment schedule will also serve as a feasibility indicator.

## Specific Aim 3

To assess the preliminary efficacy of d-DBT in improving functioning and reducing psychiatric comorbidities in individuals at CHR for psychosis in an assessor-masked preliminary RCT clinical trial. **H3**: Individuals with CHR receiving d-DBT will demonstrate enhanced resiliency, reduced depression and anxiety, personality disorder pathology, improved emotional regulation scores, reduced substance use, reduced suicidal ideation, improved functioning and cognitive performance as a result of treatment compared to CHR individuals receiving treatment as usual.

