## Outcome Assessments

**Measures/Assessment Tools:** Demographic and medical comorbidity assessments, and current medication use will be gathered at baseline. Measures will be completed at study entry and repeated immediately post-intervention at 8-weeks. Clinician rated assessments will be completed with a trained research assistant. Any changes to medication will be recorded at intervention completion. Psychiatric diagnoses will be confirmed using the Structured Clinical Interview for DSM-5 (SCID-5) and Structured Interview for Psychosis-risk Syndromes (SIPS) at baseline. Clinical assessments will be completed at baseline and 8-weeks.

Primary outcomes:

1. Feasibility outcomes will include recruitment (60 participants), retention, and completeness of modules. Completeness of modules will be assessed using a brief survey after every module and participants will receive weekly virtual check ins to help with trouble shooting and enhance engagement. Participants’ ability to complete the clinical assessment schedule will also serve as a feasibility indicator.
2. Acceptability will be informed by the Client Satisfaction Questionnaire (CSQ-8) (66). Semi-structured interviews at the end of the intervention will also provide feasibility and acceptability data.
3. System Usability Scale (SUS) (67) - assesses whether the intervention is serviceable for its intended purpose. The SUS is a reliable tool for measuring the usability. It consists of a 10-item questionnaire with five response options for respondents; from Strongly agree to Strongly disagree.

Secondary Outcomes:

1. Global Functioning: Social and Role Scales (68).
2. Psychosis spectrum symptoms: SIPS (69); PRIME-Revised (70)
3. Mood and anxiety: The State-Trait Anxiety Inventory (71), Calgary Depression Scale for Schizophrenia (72).
4. Emotion Regulation: Brief Difficulties in Emotion Regulation Scale (DERS-16) (73).
5. Substance Use: Adolescent Alcohol and Drug Involvement Scale The Timeline Follow Back (TLFB) method for measuring quantity of cannabis, alcohol, and tobacco use in the past 7 days (74); The Cannabis Use Disorders Identification Test-Revised (CUDIT-R) (75);Daily Sessions, Frequency, Age of Onset and Quantity of Cannabis Use Inventory (DFAQ-CU) (76)
6. Borderline personality dimensions: BSL-23 (77).
7. Resiliency: Connor-Davidson Resilience Scale; CD-RISC (78).
8. Suicidal ideation: Columbia-Suicide Severity Rating Scale (79).

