**Fidelity**

d-DBT will be delivered virtually in a self-led program. This eliminates the concern of inter-practitioner variability in delivering psychotherapy. There will be weekly check-ins with our research staff who will act as ‘digital navigators’ and provide non-clinical support around application use which may include application troubleshooting, guidance through application exercises, reminders, and encouragement to support engagement (81). They will have a semi-structured script which will explore if participants have been able to complete modules, explore barriers, and help answer basic questions about the content of the modules. We will also use the DBT ways of coping checklist to measure DBT-skills use (82).

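### Module completeness, a primary feasibility outcome, rests on participants' own confirmation, and the protocol names no platform record to measure or check it

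*Protocol*

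**What the plan says.** Under Outcome Assessments, the first primary outcome reads: "Feasibility outcomes will include recruitment (60 participants), retention, and completeness of modules". The same item names the measure: "Completeness of modules will be assessed using a brief survey after every module". Treatment Regimen describes that survey: at the end of each session "there will be a link to a brief survey where participants will confirm their completion of the module".

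Research staff acting as digital navigators also contact participants every week. Under Fidelity: "They will have a semi-structured script which will explore if participants have been able to complete modules". Treatment Regimen gives the purpose of this contact as "to enhance adherence and trouble-shoot any issues related to the intervention", and Participant Compliance Monitoring likewise presents it as support for retention and engagement.

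The intervention is self-led and web-based. The Background section on digital DBT says that the study group developed the platform. Treatment Regimen describes each skill as a short video, a page of key points and an interactive guided practice, and says of the homework: "These homework assignments will be embedded in the newly adapted d-DBT platform".

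Specific Aim 2 (H2) lists "attendance rates of d-DBT sessions" as evidence of acceptability without naming a data source. Statistical Methods plans a per-protocol or completers-only analysis alongside ITT.

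**The concern.** In a self-led digital programme, how much of the intervention people actually take up is a central feasibility question. Participant Compliance Monitoring itself treats poor engagement as a recognised problem in interpreting digital health research. Yet the measure fixed for this outcome depends on two things other than doing the module: whether the participant follows a link, and whether the confirmation given there is accurate.

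A participant who finishes a module and closes the browser leaves no survey. One who skips the video and the practice can still confirm. Being asked every week by staff whose task is to encourage completion may recover some missed surveys, but may also invite over-reporting. The same figure is likely to feed the H2 attendance evidence and, if completers are defined by modules done, the completers-only analysis. Usage data that are never captured cannot be recovered at the analysis stage.

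**Working it through.** **1. Which sources in the protocol bear on module completion?**

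| Source | Where | What it yields | Named as the outcome measure? |
|---|---|---|---|
| Survey after each module | Outcome Assessments; Treatment Regimen | Participant's confirmation | Yes |
| Weekly navigator script | Fidelity; Participant Compliance Monitoring | Participant's account to staff | No; its purpose is support |
| DBT ways of coping checklist | Fidelity; Schedule of Events | Skills use at follow-up | No; it does not measure modules done |
| Log-ins, video or page progress, practice or homework submission | Not mentioned | – | No |

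Both sources that touch completion are self-report, and no check against a platform record is described.

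**2. Effect of missed surveys on the count of modules.** The planned dose is 8 modules, one per week (Treatment Regimen). Let m be the share of finished modules with no survey, assumed to be 2%, 5% or 10%, with no recovery at the weekly check-in and a missing survey scored as not done. For someone who did all eight, the expected recorded count is 8 × (1 − m):

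- m = 2%: 8 × 0.98 = 7.84
- m = 5%: 8 × 0.95 = 7.60
- m = 10%: 8 × 0.90 = 7.20

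**3. Both errors together.** Let T be the true share of modules completed, FN the share of completed modules with no survey, and FP the share of uncompleted modules that are confirmed. Then observed = T × (1 − FN) + (1 − T) × FP. The assumed ranges are FN 0–20% and FP 0–30%.

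- T = 60%: lowest 0.60 × 0.80 = 48%; highest 0.60 + 0.40 × 0.30 = 72%.
- T = 80%: lowest 0.80 × 0.80 = 64%; highest 0.80 + 0.20 × 0.30 = 86%.
- T = 60% with FN = 20% and FP = 30%: 0.48 + 0.12 = 60%. The errors cancel, so the observed level gives no sign that they are there.

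**4. Comparison with the stated precision.** Sample Size and Power gives ±10.1% for adherence, retention and attrition. This reproduces as 1.96 × √(0.80 × 0.20 / 60) = 10.1%. The inputs are not unique: a proportion of 0.85 with n = 48 also gives 10.1%. Module completion exists only in the d-DBT arm, where a participant-level proportion of 0.80 has a half-width of 1.96 × √(0.16 / 30) = 14.3%, or 1.96 × √(0.16 / 24) = 16.0% after 20% dropout. All these intervals cover sampling error only. In the assumed scenarios of step 3, reporting error reaches 12 points either way at T = 60%, and from 16 points down to 6 points up at T = 80%. It would come on top of the sampling error.

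**The case against.** The other side has several sound points.

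- The survey does not stand entirely alone. A weekly staff contact that asks about completion could recover missed surveys and would shrink the figures in step 2.
- Misclassification is possible, not demonstrated. The documents give no reporting-error rate and no scoring rule for an unanswered survey.
- The numeric criteria in H2, 60 recruited and 80% retained, do not depend on the survey. Acceptability also rests on the CSQ-8, the SUS and interviews, and no stated threshold turns on module completion.
- The protocol does not define completers. The term could mean people who finish the trial, and the definition may properly sit in an analysis plan.
- A log is not error-free: a video opened is not a video watched.

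A reader might also infer that the error compounds over the course: at 98%, 95% or 90% survey response per module, only 0.98^8 = 85%, 0.95^8 = 66% or 0.90^8 = 43% of true completers would be recorded as complete. The documents do not support that reading. Nothing in them defines the outcome as all eight modules, and the calculation further assumes independent responses and no recovery at the check-in. Nor do they say that completion can already be read from the platform: embedded homework and interactive practice do not establish that activity is stored per participant.

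These points limit the size and the consequences. They do not remove the core: a primary outcome has a named measure that is self-confirmation, and no check on it.

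**Conclusion.** The point holds as a weakness in how a primary feasibility outcome is measured, fixed in the protocol's own text. It is neither a contradiction nor proof that the results will be wrong. Completion can be over- or under-recorded, and the protocol contains nothing that would show which.

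The size cannot be derived from the documents. Under the assumed missed-survey rates the loss for a true completer is modest, 0.2 to 0.8 of a module out of 8. Under the wider assumed rates for both errors, the observed share of completed modules could move by more than the stated ±10.1%. Any carry-over to the completers-only analysis is conditional on completers being defined by modules done. The trial can run as planned, but the change is worth making because it is cheap now and cannot be made retrospectively.

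**What to change.** In Outcome Assessments and Treatment Regimen, specify per-participant, time-stamped capture of module activity (skill videos opened, guided practice submitted, homework entered) and make it the primary source for module completeness. Keep the survey as a secondary self-report and report its agreement with the log. Use the same log-based measure for the attendance evidence in H2 and, if completers are defined by modules done, for the completers-only set.

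The time to do this is during the platform adaptation under Aim 1. It rests on the platform being able to record this activity, which the developers must confirm.

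Cost: some configuration and export work and a line in the consent form about usage data; no added visit, questionnaire or staff. Drawbacks: logs show activity rather than attention, and the completion figure may come out lower than self-report would give.

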**Control Group Procedures**

Participants in the control group will continue to receive treatment as usual, which may consist of routine appointments with healthcare providers, medication management, and other supportive services as deemed necessary by their care team. Outcome measures will be collected at study entry and at 8-weeks for participants in the treatment as usual group.

## Method for Assigning Participants to Treatment Groups

Participants will be randomized by a randomization schedule designed by the trial statistician to one of the two groups, d-DBT versus treatment as usual.

## Administration of Study Intervention

The d-DBT will be delivered virtually with a self-led program. Please see section 3.5 for further details.

## Participant Compliance Monitoring

Poor engagement and attrition from digital interventions is an increasingly recognized challenge for interpreting and translating the findings from digital health research. Meta-analysis has reported that 26% of individuals dropout of digital interventions for depressive symptoms (39), whereas premature termination of in person psychotherapy is estimated at 20% (40). The addition of a human component reduces attrition by more than 50% (39), therefore this study intends to use digital navigators to troubleshoot technical issues and enhance therapeutic alliance (34). Digital navigators will complete brief virtual check-ins with participants every week during the intervention. This will help enhance retention and engagement and identify any potential barriers participants are having to complete their module.

## Concomitant Therapy

Patients participating in this study will continue to be eligible for and continue their standard care, which comprises an outpatient multidisciplinary team approach including, psychiatric follow up and potential medication management. Concomitant medication/therapies will be verified with research participants at each visit. Concomitant medication analysis will be conducted using multivariate analysis to control possible effects. Receiving any additional psychotherapy interventions or structured digital mental health support during the study period is an exclusion criterion for the study.

# RESEARCH PROCEDURES

## Research Visits

The d-DBT intervention will be delivered over 8-weeks. Measures will be completed at study entry and repeated immediately post-treatment at 8-weeks. Assessments will be completed with a trained research analyst.

When possible, assessments will be done virtually. Please see schedule of events below. After informed consent has been obtained; participants will complete screening assessments to determine eligibility; followed by baseline clinical, functional, and neuropsychological assessments. The clinical, functional, and psychological assessments will be repeated approximately 8-weeks after baseline. These assessments can be scheduled on the same day or separate days depending on participant preference. If participants completed overlapping clinical, cognitive, or functional assessments as part of their participation of any CAMH study they may be shared, with participant consent. Additionally, many clinics at CAMH use certain rating scales and collect demographic, educational, and cognitive information as part of routine clinical care. For study participants where this information has already been collected as part of routine clinical care, we will endeavor to utilize this already collected information rather than repeating these assessments with participants, if the participant agrees (based on participant consent). Sharing information and assessments will reduce participant burden both by shortening research assessment duration and reducing the stress that can occur with repeated questions on the same topics. Consent for this will be obtained as part of the informed consent procedures for this study.

**Clinical Assessments**

To reduce participant burden, where possible clinical assessments will not be repeated if administered in another study (as outlined above).

**Categorical Assessments**

The Structured Clinical Interview for DSM-5 (SCID-5) (86) will be used for all participants. The SCID is a semi-structured diagnostic interview designed to assist clinicians, researchers, and trainees in making reliable DSM-5 psychiatric diagnoses. Can be administered virtually. [Approximately 60-120 minutes to complete]

**Dimensional Assessments**

*Attenuated Psychosis Symptoms*

All participants will be administered the PRIME-Revised (70). This assessment is harmonized with existing measures already utilized in several studies and clinical services at CAMH to minimize participant/patient burden [5 minutes to complete].

CHR participants will be administered the Structured Interview for Prodromal Symptoms (SIPS) (69): The SIPS is a widely used structured interview for diagnosing a CHR syndrome for psychosis and cases of first episode psychosis. It contains a severity rating scale (the Scale Of Psychosis-risk Symptoms, or SOPS), a well-anchored Global Assessment of Functioning (GAF), the DSM-IV schizotypal personality disorder checklist, a brief assessment of the family history of psychosis, and the Criteria Of Psychosis-risk Syndromes (COPS) and Presence Of Psychosis Scale (POPS) and DSM-5 Attenuated Psychosis Syndrome criterion sets. The SIPS rules in/out the current and lifetime presence of psychosis and when psychosis has never been present diagnoses three CHR syndromes. Can be administered virtually. [120 minutes to complete]

*Mood Symptoms*

Calgary Depression Scale for Schizophrenia (CDSS)(72) is a 4-point Likert type scale (0, absent; 1, mild; 2, moderate; 3, severe) with nine items. It is a reliable scale, with high internal consistency (Cronbach’s alpha = 0.855), and the CDSS is suitable for evaluating symptoms of depression in people at clinical high risk for psychosis(87). Survey administration and can be done virtually. [10 minutes to complete]

*Anxiety Symptoms*

The State-Trait Anxiety Inventory (STAI)(71) is a psychological inventory consisting of 40 self-report items on a 4-point Likert scale. The STAI measures two types of anxiety – state anxiety and trait anxiety. Higher scores are positively correlated with higher levels of anxiety. Survey administration and can be done virtually. [5 minutes to complete]

*Borderline personality dimensions*

The Borderline Symptom List (BSL-23) (77) is a well-established self-rating instrument to assess the severity of borderline typical psychopathology. The BSL-23 assesses 23 feelings and experiences typically reported by BPD patients, refers to the last week and has a range from 0 = ‘not at all’ to 4 = ‘very strong. Survey administration and can be done virtually. [10 minutes to complete]

*Emotion Regulation*

The Difficulties in emotion regulation scale (DERS)(73) is a 36-item self-report measure of six facets of emotion regulation. Items are rated on a scale of 1 (“almost never [0–10%]”) to 5 (“almost always [91–100%]”). Higher scores indicate more difficulty in emotion regulation. [5 minutes to complete]

*Functioning*

Global Functioning: Social and Role Scales - brief clinician-administered measures of social and role functioning, respectively, administered as a semi-structured interview with detailed anchors for ratings that address functional difficulties typically experienced by youth at risk for psychosis (88). Can be administered virtually. [10 minutes to complete]

*Resiliency*

The Connor-Davidson Resilience Scale (CD-RISC)(78) is a 25-item self-report rating scale designed to assess resilience, with higher scores being an indicator of high resilience. Each item is rated on a 5-point scale ranging from not true at all or zero to true nearly all the time or four. The total possible scores range from 0–100. [5 minutes to complete]

*Substance use*

Adolescent Alcohol and Drug Involvement Scale (AADIS) is a clinician rated instrument which evaluates an adolescent’s use of alcohol and other drugs (89). [5-10 minutes to complete]

The Timeline Follow Back (TLFB) ((74)) –is a self-report method for substance use, and will be used to quantify the amount/frequency of alcohol, cannabis, and tobacco in the past 7 days. [5 minutes to complete]

The Cannabis Use Disorders Identification Test-Revised (CUDIT-R) is a self-report tool developed that aim to distinguish between different levels of cannabis use, cannabis use disorders and stage of change (75). It contains 8 items, two each from the domains of consumption, cannabis problems (abuse), dependence, and psychological features. [5 minutes to complete]

The Daily Sessions, Frequency, Age of Onset and Quantity of Cannabis Use Inventory (DFAQ-CU) is a self-report tool designed to assess key dimensions of cannabis use, including the number of daily use sessions, frequency of use over time, age of first use, and quantity consumed (76). Survey administration and can be done virtually [5 minutes to complete]

*Suicide Risk*

Columbia-Suicide Severity Rating Scale (C-SSRS)(79) is a semi-structured clinical.

interview that assesses suicidal ideation severity, suicidal ideation intensity, and suicidal

behavior. It is suited to use in youth at risk for psychosis. [10 minutes to complete]

*Neurocognitive Domains*

The MATRICS Consensus Cognitive Battery (MCCB) (80) is intended to provide a relatively brief evaluation of key cognitive domains relevant to schizophrenia and related disorders. The MCCB includes ten tests that assess seven cognitive domains: (1) speed of processing; (2) attention/vigilance; (3) working memory; (4) verbal learning; (5) visual learning; (6) reasoning and problem solving; and (7) social cognition. Requires in person administration for standardization. HVLT, Maze, and BVMT forms will be counterbalanced at baseline and follow-up. [60 minutes to complete]

